**Reason for ED presentation/ICU admission**		
Sepsis,* n (%)*		
Trauma,* n (%)*		
Respiratory distress,* n (%)*		
Respiratory distress syndrome (RDS)/hyaline membrane disease (HMD),* n (%)*		
Meconium aspiration syndrome (MAS),* n (%)*		
Apnoea,* n (%)*		
Airway obstruction,* n (%)*		
Altered level of consciousness,* n (%)*		
Seizures,* n (%)*		
Overdose/intoxication,* n (%)*		
Congenital heart disease,* n (%)*		
Heart failure,* n (%)*		
Congenital abnormality,* n (%)*		
Malignancy,* n (%)*		
Pre-operative ICU admission,* n (%)*		
Post-operative ICU admission,* n (%)*		
Burns,* n (%)*		
Others,* n (%)*		
**Indication for intubation**		
Inadequate oxygenation,* n (%)*		
Inadequate ventilation,* n (%)*		
Unprotected airway,* n (%)*		
Haemodynamic instability,* n (%)*		
Procedure/intervention required,* n (%)*		
Expected clinical deterioration,* n (%)*		
Failed extubation,* n (%)*		
Upper airway obstruction,* n (%)*		
Others,* n (%)*		
**Pre-intubation observations**		
SpO_2_ * mean (SD)/median (IQR)*		
Hypotension, *n (%)*		
Heart rate centile		
< 10th centile,* n (%)*		
10–90th centile,* n (%)*		
> 90th centile,* n (%)*		
Respiratory rate centile		
< 10th centile,* n (%)*		
10–90th centile, *n (%)*		
> 90th centile,* n (%)*		
**Respiratory support, prior to intubation**		
Room air/nil support,* n (%)*		
Standard oxygen therapy, *n (%)*		
Nasal high flow, *n (%)*		
Bag-mask system,* n (%)*		
Non-invasive ventilation,* n (%)*		
Laryngeal mask airway, *n (%)*		
**Pre-oxygenation technique**		
Room air/nil support,* n (%)*		
Standard oxygen therapy, *n (%)*		
Nasal high flow, *n (%)*		
Bag-mask system,* n (%)*		
Non-invasive ventilation,* n (%)*		
Laryngeal mask airway, *n (%)*		
**Operator level for first intubation attempt** ^**a**^ **,** * n (%)*		
Consultant		
Fellow or registrar		

*SD* standard deviation, *IQR* interquartile range, *ED* emergency department, *ICU* intensive care unit, *ET* endotracheal tube

^a^Used for stratification

##### Secondary outcome measures

Binary outcome measures (e.g. occurrence of AE) will be treated in the same manner as the primary outcome; however, no *p*-values will be reported (Table 3). Similar analyses will be undertaken for continuous outcomes: linear regression with adjustment for the treatment group and stratification variables as fixed effects and site and patient as random effects, with reporting of mean difference (unadjusted for stratification variable and adjusted) and 95% CIs. If necessary, quantile regression will replace linear regression in the instance of highly skewed data. Survival outcomes (length of PICU stay, length of hospital stay) will be visually presented using a Kaplan–Meier plot, and a Cox proportional hazard model will be used to assess the differences between the treatment groups with treatment group and stratification variables as fixed effects and site and patient as random effects (i.e. utilising a shared frailty model). The proportionality assumption will be inspected visually using Kaplan–Meier plots and the log–log plot. The hazard ratio and 95% CI will be presented as an estimate of treatment effect. Competing-risk regression will be used to analyse VFDs (competing risk of mortality with duration of ventilation). The lowest oxygen saturation during each intubation encounter will be reported in-text using each encounter as the unit of analysis (and as such incorporating intubation episode as a further random effect into the model). Key assumptions of the models (for logistic regression: specification, goodness-of-fit, absence of multicollinearity and absence of influential observations; for survival analysis: proportionality assumption, goodness-of-fit; for linear regression: specification, distribution of residuals, homoscedasticity, absence of multicollinearity, linearity) will be tested and reported on.

**Table 3 Tab3:** Primary outcomes in the total trial cohort and subgroups as per intention-to-treat analysis

	**Standard care, ** ***N*** ** = **	**THRIVE, = **	**Estimate of difference (95% CI)***	**Adjusted estimate of difference (95% CI)** ^**a**^	***p*** **-value**
**Outcome: hypoxic event** *Oxygen saturations (SpO* _*2*_ *) of* ≤ *90% or a SpO* _*2*_ * saturation difference* ≥ *10% for patients with cyanotic congenital heart disease with known substantial right-to-left shunts*					
**Total trial cohort,** * n (%)*					

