### Statistical principles

The primary analysis will be conducted based on the intention-to-treat principle. Specifically, each randomised intubation encounter will be analysed based on the allocated treatment group, independent of compliance with the treatment delivered.

A per-protocol analysis including all intubation attempts where a study therapy was commenced (regardless of whether it was the therapy that was randomised) will also be undertaken and reported in the supplementary material.

The unit of analysis for most outcomes is the intubation encounter. If patients are required to be intubated more than once, they can be re-enrolled and re-randomised, theoretically receiving different study interventions for each intubation attempt within a single admission. For secondary outcomes relating to admission (i.e. ventilator-free days, length of ICU and hospital stay and death), only those patients with one enrolment per admission will be included in the primary and per-protocol analyses.

Statistical tests will be two-sided applying a statistical significance level of 0.05, although the primary outcomes will be analysed at a level of 0.025 (applying Bonferroni’s correction). We will not apply a formal correction for multiple testing to any of the subgroup analyses, sensitivity analyses or to the secondary outcomes. We will ensure conclusions drawn as a result of analyses are interpreted with deference to multiple comparisons.

If there is more than 10% of data missing for the primary outcomes, a sensitivity analysis using multiple imputation will be undertaken.

Continuous variables will be assessed for normality; this will be undertaken using visual inspection of histograms and *Q*-*Q* plots.

Descriptive statistics will be used when summarising variables; frequencies (percentages) for discrete variables, mean and standard deviation (SD) for normally distributed continuous variables, or, if continuous variables are non-normally distributed, median with interquartile range (IQR).

Subgroup analyses will be executed regardless of any potential treatment effect on the primary or secondary outcomes in the main cohort.

Changes to the analysis plan by the investigators effective after the publication of this SAP will be declared as such.

The statistical analysis will be undertaken using StataSE version 17 (StataCorp Pty Ltd., College Station, TX).

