## List of planned Appendix material

- Data and Safety Monitoring Board terms of reference/charter
- Monitoring plan
- Enrolment statistics by month, site, and country
- Results of interim analyses
- Neonatal characteristics of participants enrolled in at a neonatal intensive care unit site or aged < 28 days at time of intubation
- Kaplan–Meier survival curves for length of PICU stay and length of hospital stay
- Forest plot of the treatment effect across subgroups for the primary and secondary outcomes
- Results of per-protocol analysis
- Results of sensitivity analysis
- List of protocol deviations
- List of adverse events

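### Length of ICU and hospital stay are given Kaplan–Meier plots and a Cox model with no rule for deaths, although mortality is treated as a competing risk for ventilation

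*SAP article*

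**What the plan says.** In the SAP article, Outcome definitions, both stays run from successful intubation to discharge, from the ICU in one case and from hospital in the other. Neither definition mentions death. In the same list, ventilation-free days do have a death rule (zero if the child died within 28 days of randomisation), and death during the admission is itself a secondary outcome.

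Under Secondary outcome measures the display is fixed: "Survival outcomes (length of PICU stay, length of hospital stay) will be visually presented", by a Kaplan–Meier plot. So is the effect estimate: "a Cox proportional hazard model will be used to assess the differences between the treatment groups", with a shared-frailty structure and a hazard ratio. The same paragraph then gives ventilation-free days a competing-risk regression, for the stated reason "competing risk of mortality with duration of ventilation". The List of planned Appendix material repeats the choice of display: "Kaplan–Meier survival curves for length of PICU stay and length of hospital stay".

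Deaths stay in the analysis set. Statistical principles says of the admission-level outcomes that "only those patients with one enrolment per admission will be included in the primary and per-protocol analyses". The notes to Table 4 restrict the stay outcomes by enrolment and by ICU admission, not by survival.

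**The concern.** A child who dies in the unit or in hospital can never be discharged alive, so death competes with discharge just as it competes with the end of ventilation. The plan recognises this for ventilation-free days but not for the two stays. Because it names the estimators for the stays, this is a choice made in the SAP and not a detail left to the protocol.

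Two things are at stake. First, the published curves: the Kaplan–Meier method with deaths censored describes discharge as if death could not occur, so it shows more children going home than do. Second, the meaning of the hazard ratio: with the coding of deaths unstated, the same Cox model can estimate different quantities, and the coding could be chosen after the data are seen. Length of stay in intensive care is one of the stated secondary objectives.

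**Working it through.** The SAP gives no mortality rate and no expected length of stay, so there is no figure of its own to reproduce. Every size below rests on assumptions.

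**Step 1. Curves, constant hazards.** Assume a discharge hazard λ = 1/7 per day (mean 7 days to discharge if nobody died) and eventual in-hospital mortality m. The death hazard is μ = λm/(1 − m), so that μ/(λ + μ) = m. At day 28, λ × 28 = 4 and (λ + μ) × 28 = 4/(1 − m).

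- Deaths censored: 1 − KM = 1 − exp(−4) = 0.982, whatever m is.
- Cumulative incidence of discharge alive: (1 − m) × [1 − exp(−4/(1 − m))].
- Death counted as end of stay: 1 − exp(−4/(1 − m)).

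| Assumed mortality | 1 − KM, deaths censored | Discharged alive | Overstatement (points) | Death as end of stay |
|---|---|---|---|---|
| 2% | 0.982 | 0.963 | 2 | 0.983 |
| 5% | 0.982 | 0.936 | 5 | 0.985 |
| 10% | 0.982 | 0.889 | 9 | 0.988 |
| 15% | 0.982 | 0.842 | 14 | 0.991 |

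Worked line for 10%: 4/0.90 = 4.444; 1 − exp(−4.444) = 0.988; 0.90 × 0.988 = 0.889.

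Median stay at 10% mortality: 7 × ln 2 = 4.85 days with deaths censored; 0.90 × 4.85 = 4.37 days with death as end of stay; 5.11 days as the time by which half of all children have been discharged alive.

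**Step 2. Curves, a different shape.** A simulation assumed log-normal stays (median 8 days, log-SD 0.9) and a median time to death of 5 days. At mortality of 3%, 6% and 10%, 1 − KM at day 28 was 91.4%, 91.1% and 90.5%, against 89.0%, 86.3% and 82.5% discharged alive. The gaps are 2.4, 4.8 and 8.0 points, so the pattern does not depend on constant hazards.

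**Step 3. Hazard ratio, THRIVE v control.** Keep the discharge hazard equal in both arms and let mortality be 10% in control and 5% in THRIVE.

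- Deaths censored: the cause-specific ratio is λ/λ = 1.00.
- Death as event: (λ + μ₁)/(λ + μ₀) = (1/0.95)/(1/0.90) = 0.90/0.95 = 0.947. Fewer deaths look like a slightly longer stay.
- Subdistribution scale (deaths kept at risk): about 1.12 by simulation.

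With mortality reversed (5% v 10%), the three are 1.00, about 1.05 and 0.90.

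With the log-normal stays of step 2, identical survivors' stays and death as event, 10% v 5% mortality gave 0.964, 0.979 and 0.998 for median times to death of 3, 5 and 8 days. Mortality of 3% v 1.5% gave 0.993 to 0.997. With equal mortality the ratio is about 1.00.

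**The case against.** The strongest reply is that the plan never says how deaths are coded. A reader might infer that it treats deaths either as future discharges or as short stays, but that inference only covers the two usual codings. A third, keeping deaths at risk or assigning them the longest stay, is possible. A condensed article may also leave coding to a fuller document. This stands as a limit on the claim: the text supports that the handling of death is unstated and that the named display is unsuitable under either usual coding. It does not support that a particular wrong coding has been adopted.

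A reader might also infer that the Cox model is wrong whichever way deaths are coded. That is too strong. With deaths censored it validly estimates the cause-specific hazard ratio for discharge. Ending the stay at death is likewise a coherent measure of bed use, though not of recovery.

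A third tempting reading is that the treatment comparison is materially biased, with an arm that has more early deaths appearing to have shorter stays. That needs a mortality difference between arms. The intervention is oxygen during the apnoeic period of an intubation, and nothing in the SAP anticipates such a difference. With similar mortality the curves are overstated about equally in both arms and the ratio does not move. Deaths are also reported by arm in Table 4 beside the stay outcomes, which partly guards against misreading.

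These points limit the size. They do not remove the inconsistency with the plan's own treatment of ventilation-free days, or the bias of the Kaplan–Meier curve when deaths are censored.

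**Conclusion.** The point holds in limited form. The plan assigns two outcomes that death can prevent to Kaplan–Meier plots and a Cox model, with no rule for deaths, in the same paragraph that treats mortality as a competing risk for ventilation-free days.

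The clear fault is in the curves. With deaths censored, they overstate discharge alive at day 28 by an amount close to the mortality rate: about 2 points at 2% and about 14 points at 15%, under an assumed mean of 7 days to discharge. The hazard ratio is a matter of interpretation more than error. With deaths censored it is cause-specific and must not be read as an effect on the probability of, or time to, discharge alive. With death as the end of stay it shifts only if mortality differs, to about 0.95 to 1.00 for assumed 10% v 5%.

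Neither primary outcome is touched, and Table 4 reports these secondary outcomes without p-values. The correction is worth making before analysis because the choice of coding should not be open once the data are seen.

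**What to change.** In Outcome definitions and Secondary outcome measures, state that the event for both stays is discharge alive, with death before discharge as a competing event.

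Replace the Kaplan–Meier plots, there and in the List of planned Appendix material, with cumulative incidence (Aalen–Johansen) curves of discharge alive by arm. The log–log plot can stay as a check on the cause-specific model.

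For the effect estimate, do one of the following:

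- Keep the Cox shared-frailty model, described as the cause-specific hazard of discharge alive with deaths censored, and report the cause-specific hazard ratio for death beside it. This preserves the planned random effects.
- Add the competing-risk regression already planned for ventilation-free days, and say how clustering by site is handled, for example by robust standard errors.

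Confirm that the timing of each in-hospital death is recorded. The 28-day rule for ventilation-free days implies that timing is known to that extent, but the document does not say that dates of death are collected.

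The cost is a change of SAP wording and a little more analysis work, declared as a change made after publication of the SAP. Design and sample size are unaffected.

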**Subgroup: patient age^**					
< 1 year,* n (%)*					
1–7 years,* n (%)*					
> 7 years,* n (%)*					
**Subgroup: operator level^**					
Junior, *n (%)*					
Senior,* n (%)*					
**Subgroup: location of intubation^**					
Emergency department,* n (%)*					
Paediatric Intensive Care Unit,* n (%)*					
Neonatal intensive care unit,* n (%)*					
**Outcome: successful first attempt intubation** *First attempt without any hypoxemia (SpO* _*2*_ ≤ *90% or saturation difference* ≥ *10% for right-to-left shunt)*					
**Total trial cohort,** * n (%)* ^a,^*					
**Subgroup: patient age^**					
< 1 year,* n (%)*					
1–7 years,* n (%)*					
> 7 years,* n (%)*					
**Subgroup: operator level^**					
Junior, *n (%)*					
Senior,* n (%)*					
**Subgroup: location of intubation^**					
Emergency department,* n (%)*					
Paediatric intensive care unit,* n (%)*					
Neonatal intensive care unit,* n (%)*					

*IQR* interquartile range, *CI* confidence interval

^*^Adjusted for study site and patient only; *p*-value = xx

^a^Adjusted for age at randomisation, operator level, study site and patient

^*p*-value represents interaction term

We will undertake the following subgroup analyses (Table 2):Age group at randomisation (stratification variable; pre-planned)Operator level (stratification variable; pre-planned)Location of intubation (ED, PICU or NICU; defined after commencement of trial)

All subgroup analyses will examine the primary outcome only. Subgroup analyses will be undertaken using the same analysis methods described for the primary outcome measure, with the addition of the subgroup variable and its related interaction term into the main regression model; the interaction effect (and 95% CI and *p*-value) will be reported, alongside the descriptive statistics for the outcome under investigation. A forest plot will be developed to present heterogeneity between the treatment group and subgroup variable, including the *p*-value, and presented. Additionally, a sensitivity analysis will be undertaken based on the lowest SpO_2_ during intubation (< 80%; ≥ 80%).

#### Missing data

The primary outcome for this study is recorded by two methods, paper CRF and video recording, as such it is expected that there will be very few participants with missing primary outcome data. Where the data is not recorded on either the paper CRF or video, the medical record will be used to source the required data. As such, multiple imputation will only be undertaken if > 10% of the primary outcome data is unavailable and reported as sensitivity analysis. The fully conditional specification will be used for imputation; the imputation model will include randomised treatment arm, study site and the stratification variable. Ten sets of imputed data will be created using the methods described for the primary outcome. A pooled common effect estimate and 95% confidence interval will be generated from the imputed datasets.

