### Sample size

A conservative estimate of the primary outcome of hypoxaemia is set at 16%, following an unpublished 2016 audit of data from the Queensland Children’s Hospital, which we found was comparable to a published report [1]. Assuming a clinically relevant effect size of a 50% reduction in the proportion of desaturation events from 16 to 8%, along with a type I error of 0.025 (adjusting for two primary outcomes using Bonferroni’s correction) and power of 90%, 816 intubation encounters in total are required. Successful first-attempt intubation, the second primary outcome, assumes an absolute increase from 60 to 80%, requiring 258 intubation encounters. Allowing for 15% attrition, the total sample size that will satisfy both primary outcome measures is 960 intubation encounters. An attrition rate of 15% was selected based on the assumption that a proportion of patients enrolled will have a clinical deterioration, or other clinical events, during a high-stress procedure leading to the inability to deliver the intervention or collect the outcome data required for the study.

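### Primary outcomes lost because the child deteriorated are not tested at any level of missing data: the only missing-data sensitivity analysis is an imputation on arm, site and strata, run only above 10% missing

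*SAP article*

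**What the plan says.** The Sample size section of the SAP article allows for 15% attrition. Its reason is that "a proportion of patients enrolled will have a clinical deterioration, or other clinical events, during a high-stress procedure leading to the inability" either to deliver the allocated intervention or to collect the outcome data. The requirement of 816 encounters is raised to 960 on that basis.

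The Missing data section takes a more optimistic view: "it is expected that there will be very few participants with missing primary outcome data". Its grounds are that the primary outcome is captured on the paper CRF and on video, with the medical record as a third source. It then sets the rule: "multiple imputation will only be undertaken if > 10% of the primary outcome data is unavailable", reported as a sensitivity analysis. The imputation model is listed as treatment arm, study site and the stratification variable, with ten imputed sets. The Statistical principles section repeats the 10% threshold.

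One other sensitivity analysis is named, at the end of the subgroup text. It splits on lowest SpO2 at 80% and does not concern missing data.

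**The concern.** The SAP itself identifies a mechanism by which the primary outcome goes missing: the child deteriorates during the procedure. The outcome is hypoxaemia during the same procedure, so outcomes lost in this way are unlikely to resemble the observed ones. Three features of the rule leave this untested.

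- The trigger is the amount missing. It ignores why outcomes are missing and whether the loss is balanced between arms.
- At or below the trigger, encounters without an outcome leave the analysis and no check is specified.
- Above the trigger, the imputation assumes data missing at random given arm, site and strata. Those are essentially the covariates already in the primary model, so the imputed result should sit close to the complete-case result. It cannot show what happens if the missing children did worse.

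At stake is whether a positive hypoxaemia result could be defended if a modest number of outcomes were lost unevenly.

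**Working it through.** **Inputs from the SAP.** Planned effect on hypoxaemia: "50% reduction in the proportion of desaturation events from 16 to 8" per cent. Second primary outcome: "assumes an absolute increase from 60 to 80%, requiring 258 intubation encounters". Level: "type I error of 0.025 (adjusting for two primary outcomes using Bonferroni’s correction"). Power 90%, allocation 1:1, attrition 15%. Sidedness: "Statistical tests will be two-sided".

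**Step 1: reproduce the plan's figures.** Per arm, n = [z₁√(2p̄(1−p̄)) + z₂√(p₁(1−p₁)+p₂(1−p₂))]² / (p₁−p₂)², with z₁ = 2.2414 (two-sided 0.025) and z₂ = 1.2816.

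- 16% v 8%: 407.3, rounded up to 408, so 816 in total.
- 60% v 80%: 128.04, rounded up to 129, so 258 in total.
- 816 / (1 − 0.15) = 960.

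All three agree with the SAP. The inflation treats all 960 − 816 = 144 encounters as giving no outcome.

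**Step 2: what can go missing without any check.** The rule needs more than 10%, so up to 0.10 × 960 = 96 encounters (48 per arm if balanced).

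**Step 3: hypoxaemia at 9% missing.** Per arm: 480 randomised, 43 missing, 437 observed. Observed events: 437 × 0.16 = 69.92 in control and 437 × 0.08 = 34.96 in THRIVE. Add 43 × (assumed rate among the missing), divide by 480, and test with z = (p₁−p₂)/√(2p̄(1−p̄)/480). The rates among the missing are assumptions.

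| Missing control | Missing THRIVE | Events, control v THRIVE | Rates | p |
|---|---|---|---|---|
| 16% | 30% | 76.80 v 47.86 | 16.0% v 10.0% | 0.005 |
| 16% | 50% | 76.80 v 56.46 | 16.0% v 11.8% | 0.058 |
| 30% | 60% | 82.82 v 60.76 | 17.3% v 12.7% | 0.046 |
| 16% | 100% | 76.80 v 77.96 | 16.0% v 16.2% | 0.92 |
| 50% | 50% | 91.42 v 56.46 | 19.0% v 11.8% | 0.002 |
| 100% | 100% | 112.92 v 77.96 | 23.5% v 16.2% | 0.005 |

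Second row in full: p̄ = (76.80 + 56.46)/960 = 0.1388; standard error = √(2 × 0.1388 × 0.8612/480) = 0.0223; z = 0.0424/0.0223 = 1.90.

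**Step 4: where the conclusion turns.**

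- At 10% missing (432 observed, 48 missing per arm) with missing controls at 16%, significance at 0.025 is lost when about 39% of missing THRIVE encounters are hypoxaemic: (432 × 0.08 + 48 × 0.39)/480 = 11.1% v 16.0%, p = 0.027.
- In the extreme bound (no missing control hypoxaemic, every missing THRIVE encounter hypoxaemic), significance is lost from about 2.9% missing. The difference is zero when 0.16(1−m) = 0.08(1−m) + m, so m = 0.08/1.08 = 7.4%.

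**Step 5: successful first attempt, worst case at 10% missing.** Control (432 × 0.60 + 48)/480 = 64%; THRIVE (432 × 0.80)/480 = 72%; p = 0.008. The conclusion stands.

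**The case against.** **The 15% and the expectation of few missing outcomes need not conflict.** A reader might infer that the SAP forecasts 15% missing outcomes in one section and denies it in another. The text does not support that. The 15% also covers failure to deliver the intervention, and under the intention-to-treat rule in Statistical principles such encounters keep their outcome. No split is given, so the 15% is an upper planning allowance. If all 15% did lose their outcome, the trigger would be met and imputation would run. This stands: the two sections need reconciling, but they are not strict opposites.

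**Safeguards exist.** There are three data sources, and the Data monitoring section plans verification of outcome items and video review for every enrolled patient. The CONSORT diagram is to show documentation of the primary outcome by arm. This makes 9% missing an assumption and possibly a pessimistic one. It does not remove the gap: Outcome definitions requires a bedside-monitor reading with an accurate trace, and where the trace is poor all three sources may lack a valid value.

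**A loss of up to 10% does not by itself erase the effect.** A reader might infer that it does because 10% exceeds the planned 8 points. That compares a share missing with a risk difference. The effect is lost only if missing THRIVE children are much more often hypoxaemic than missing controls, and nothing in the SAP says that they would be. With equal rates among the missing in both arms, the result holds. At about 3% missing (14 per arm), even all missing THRIVE encounters hypoxaemic against 16% in controls leaves p = 0.015. This stands, and it limits the size of the point.

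**Conclusion.** The point holds as a weakness in the missing-data rule. The sole missing-data sensitivity analysis is absent at or below 10% missing. Above 10% it rests on an assumption that the SAP's own account of attrition calls into question. Outcome-related loss is therefore untested at any level.

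Its size is conditional. For hypoxaemia at 9% missing, the finding at 0.025 is lost under strongly arm-differential loss (p = 0.058 and 0.046 in two such cases, no difference in a third) and kept when the missing have the same event rate in both arms (p = 0.002 and 0.005). It does not extend to successful first attempt, which survives the worst case at 10% missing.

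The figures assume the planned rates among observed encounters, 480 per arm, equal numbers missing, and a pooled two-sample test without the planned covariates and random effects. They treat the assumed events as known, so a full analysis would carry somewhat more uncertainty. This is a change that should be made; it does not make the primary analysis invalid.

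**What to change.** In the Missing data section, and in the matching sentence of Statistical principles:

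1. Remove the 10% trigger as the condition for any sensitivity analysis. Whenever a primary outcome is missing, report the number and the reason by arm.
2. Run a tipping-point analysis, or at least best and worst cases, over the event rate among the missing in each arm separately. Include the case in which outcomes lost through deterioration count as hypoxaemia, and so as first-attempt failure.
3. Keep multiple imputation as an additional analysis and state its missing-at-random assumption.
4. In Sample size, state how much of the 15% is lost outcome data and how much is non-delivery, and align this with the expectation in Missing data.

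The cost is a few sentences and a short computation on data already collected. The SAP already provides for declaring changes made after publication. The downside is that the extra analysis may show the hypoxaemia result to be less robust than the complete-case figure suggests.
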